#### **10.1.2. Severity, relationship of event to study drug, and outcome**

The severity of a clinical adverse event is to be scored according to the following scale:

|   |                  |                                                                 |
|---|------------------|-----------------------------------------------------------------|
| 1 | Mild             | Awareness of sign or symptom, but easily tolerated              |
| 2 | Moderate         | Discomfort enough to cause interference with usual activity     |
| 3 | Severe           | Incapacitating with inability to work or perform usual activity |
| 4 | Life-threatening | Patients at risk of death at the time of the event              |

The relationship of an adverse event to study drug is to be assessed according to the following definitions and can only be done by the study physician:

- 1      **Definitely unrelated**  
It should be reserved for those events which cannot be even remotely related to study participation (e.g. injury caused by a third party).
- 2      **Unlikely**  
There is no reasonable temporal association between the study drug and the suspected event and the event could have been produced by the subject's clinical state or other modes of therapy administered to the subject.
- 3      **Possible**  
The suspected adverse event may or may not follow a reasonable temporal sequence from study drug administration but seems to be the type of reaction that cannot be dismissed as unlikely. The event could have been produced or mimicked by the subject's clinical state or by other modes of therapy concomitantly administered to the subject.
- 4      **Likely**  
The suspected adverse event follows a reasonable temporal sequence from study drug administration, abates upon discontinuation of the drug, and cannot be reasonably explained by the known characteristics of the subject's clinical state.
- 5      **Definitely related**  
It should be reserved for those events which have no uncertainty in their relationship to test drug administration: this means that a re-challenge was positive.

The outcome of each AE must be assessed at the same visit and according to the following classification:

- |                                  |                                                                                                         |
|----------------------------------|---------------------------------------------------------------------------------------------------------|
| - Completely recovered :         | The patient has fully recovered with no observable residual effects                                     |
| - Not yet completely recovered : | Improvement in the patient's condition has occurred, but the patient still has some residual effects    |
| - Deterioration :                | The patient's overall condition has worsened                                                            |
| - Permanent damage :             | The AE has resulted in a permanent impairment                                                           |
| - Death :                        | The patient died due to the AE                                                                          |
| - Ongoing :                      | The AE has not resolved and remains the same as at onset                                                |
| - Unknown :                      | The outcome of the AE is not known because the patient did not return for follow-up (lost to follow-up) |

Changes in the severity of an AE will be documented to allow an assessment of the duration of the event at each level of intensity. Adverse events characterized as intermittent require documentation of onset and duration of each episode.

The investigator is obliged to assess the relationship between investigational product and the occurrence of each AE/SAE. The investigator will use clinical judgement to determine the relationship. Alternative causes, such as natural history of the underlying diseases, concomitant therapy, other risk factors, and the temporal relationship of the event to the NuvaRing® will be considered and investigated.

#### **10.1.3. Adverse Event Management**

Participants will be asked to inform the study staff of any medical problems while they are taking part in the study. Participants will be provided with contact information and instructions to contact the study physician or designee to report any AEs they may experience. AEs will be collected until the final ring removal visit and may also be identified during laboratory testing, medical histories and physical examinations. Treatment for AEs possibly/probably/definitely related to study participation will be provided by the study clinic, to the extent possible, at no cost to the participant.

All clinical and laboratory toxicities will be managed according to standard medical guidelines.

All AEs will be followed up until resolution.

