- The pelvic and general physical examinations will be performed as at baseline. A total of 3 vaginal swabs are collected for:
  - One cotton swab for Wet Mount [*Trichomonas vaginalis* (TV); *Candida albicans*] and smears for BV diagnosis;
  - Two regular flocked swabs (Copan, Italy) for the characterisation of the vaginal microbiome.
- At visit 6 for Group A and visit 5 for Group B, after the final ring has been removed and all other vaginal specimens have been collected, a CVL sample will be collected.
- A urine sample is obtained, tested for pregnancy and an aliquot of fixated urine will be stored for FISH analysis.
- A completed diary card will be collected at each visit and a new diary card will be provided. Any problems with ring use will be addressed.
- The removed ring will be processed according to the instructions provided by the ITM and stored for biofilm analysis.
- Risk reduction counselling will be provided as well as condoms (free of charge).
- During the last ring removal visit (V6 for group A and V5 for group B) the following additional procedures will be offered:
  - a Visual Inspection with Acetic acid (VIA) to identify women at risk for cervical cancer;
  - An HIV test according to the national HIV algorithm. A maximum of 5 ml of blood will be collected by venepuncture in a serum tube. Pre- and post-test HIV counselling will be provided.

Additional questionnaires during ring removal visits:

1. The IAQ will be performed at every visit and will assess adherence and acceptability of the ring use but will be more comprehensive at visits 4 and 6 for group A and at visits 3 and 5 for group B. It will also assess factors that might influence the vaginal microbiome and vaginal inflammation.
2. Between weeks 7 and 9, 16-24 women will be enrolled in one of two FGD in each randomization group, for a total of four FGD.

3. At the last ring removal visit, and if funding permits, all study participants will be invited to provide their feedback on experiences with the new contraceptive method, on acceptability and adherence using ACASI.

The following procedures are performed at the ring insertion visits for group A:

- Information on adverse events, social harms and concomitant medication will be collected.
- Risk reduction counselling will be provided as well as condoms (free of charge).

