#### **8.1.4. Final Study Visit**

At the last visit for both groups at week  $14 \pm 3$  days, a sub-sample of women will be invited to participate in IDIs (3-5 women) and FGDs (8-12 women in each group) until data saturation is reached. Women participating in IDIs will be purposively selected among women who agreed to participate in IDIs and according to age/parity and experience with contraception in order to have a wide variation of key characteristics and experiences.

Women participating to FGDs will be purposively selected among women participating in the clinical trial and who have previously accepted to be included in the qualitative research, according to the same criteria as IDIs, i.e. age/parity and experience with contraception.

IDIs will also be conducted with male partners ( $n=5$  in each randomization group). Women who participated to the after-trial FGD or IDIs will invite their partner to participate in IDIs. Those who agree to participate will be included in the end trial IDIs to reach a sample of 5 in each randomization group.

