#### **10.1.5. Serious Adverse Events (ICH E6, Section 1.50)**

An SAE is any adverse event/experience occurring at any study drug dose that results in any of the following outcomes:

- Death;
- Life threatening (subject at immediate risk of death);
- Requires in-patient hospitalization or prolongation of existing hospitalization;
- Results in congenital anomaly/birth defect;
- Results in a persistent or significant disability or incapacity.

An important medical event that may not result in death, be life threatening, or require hospitalization may be considered an SAE when, based upon appropriate medical judgment, the event may jeopardize the subject and may require medical or surgical intervention to prevent one.

There may be situations when an SAE has occurred and the investigator has minimal information to include in the initial report to the Sponsor. However, it is very important that the investigator always makes an assessment of causality for every event prior to transmission of the report to the Sponsor according to the definitions in section 10.1.2. The investigator may change his/her opinion of causality in light of follow-up information, amending the SAE-report form accordingly.

All SAE's whether or not deemed drug related or expected must be reported immediately or within 24 hours (one working day) using the SAE Notification Form by telefax or email to:

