#### **11.1.1. Study Objectives and Variables of Interest**

The primary and secondary objectives of this clinical trial are to assess the impact on the vaginal microbiome of the use of a vaginal ring intermittently (3 weeks followed by 1 week off) or continuously (primary objective), to assess the general safety of the CVR (secondary objective 1), to assess vaginal biofilm formation and, to detect the presence or absence of a biofilm on the CVRs after intermittent or continuous use (secondary objective 2), and to determine the impact of intermittent or continuous use of the CVR on markers of inflammation and immune activation in the vagina (secondary objective 3).

The objectives will be reached by describing and comparing the variables of interest in women randomized to either intermittent vaginal ring use (group A) over a 12 week study period or continuous ring use (group B) over a 13 week study period.

The variables of interest are:

*Primary:* Changes from baseline (pre-ring use) in vaginal bacterial counts and in the absence/presence of BV-related bacteria as measured with quantitative real time PCR. Specifically, the flora species under study will include (but may not be limited to) the following species

- a. Total *Lactobacillus* count
- b. *Lactobacillus crispatus*
- c. *L. iners*
- d. *L. jensenii*
- e. *L. gasseri*
- f. *L. vaginalis*
- g. *Atopobium vaginae*
- h. *Gardnerella vaginalis*

*Secondary:*

1. Incidence of self-reported vaginal symptoms and clinician-observed signs  
Specifically:
  - a. Incidence of self-reported urogenital symptoms: any ring-use emergent cases of irritation, burning, itching, discharge, bleeding, pain
  - b. Incidence of genital signs on examination: any ring-use emergent cases of vaginal discharge, erythema, edema, ulcer, condyloma, petechia, ecchymosis, peeling
2. Incidence of BV as defined as a Nugent score >6
3. The numbers of women prematurely withdrawing from the study or discontinuing ring use
4. Incidence of adverse experiences during ring use and serious adverse experiences during or within 7 days after ring use
5. The numbers of incident STIs (HIV, HSV-2, Syphilis, Trichomoniasis, Chlamydia, Gonorrhea) and candidiasis
6. Nugent scores and Ison & Hay grading of the vaginal flora
7. Changes in phenotype of BV-related bacteria: specifically
  - i. Presence of dispersed forms of bacteria
  - ii. Presence of adhesive forms of bacteria on epithelial cells

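### The serious-event endpoint extends 7 days past ring use, but planned adverse-event collection ends at the last ring removal, leaving that final week to passive reporting

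*Protocol*

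**What the plan says.** Three parts of the Protocol bear on this.

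- **Endpoint.** Section 11.1.1, secondary variable 4: "Incidence of adverse experiences during ring use and serious adverse experiences during or within 7 days after ring use". The window is ring use for adverse events in general, and ring use plus 7 days for serious ones. The synopsis and section 6 name the endpoint without a window, so 11.1.1 is the only place that fixes it. Section 11.1.2.4 compares adverse experiences between the randomized groups over the full study period with Fisher's exact test.
- **Collection period.** Section 10.1.3: "AEs will be collected until the final ring removal visit". Section 10.1.5 gives serious events no collection period of their own and defines them as a kind of adverse event: "An SAE is any adverse event/experience occurring at any study drug dose".
- **Schedule.** In section 8.1.8 the entry for concomitant medication and adverse events appears for the last time at V6, week 12 (group A) and V5, week 13 (group B), which are the final ring removals. The week-14 row shows only FGD/IDI in both groups. Section 8.1.4 describes that visit in the same terms: "a sub-sample of women will be invited to participate in IDIs (3-5 women) and FGDs (8-12 women in each group". It mentions no safety procedure.

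For women who stop early, section 8.1.7 provides for the procedures of the last ring removal visit.

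**The concern.** An endpoint window has to be matched by a collection period at least as long. Here the endpoint asks for one more week of serious events than the plan sets out to collect. If the last week rests on women coming forward, serious events in it may be missed, and whether they are found depends on who happens to make contact.

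This matters for two reasons. The endpoint is prespecified and will be compared between groups. Also, section 10.2 replaces a formal monitoring board with one independent safety monitor, who depends on serious-event reports and is to give special attention to cardiovascular events such as venous thrombosis. The statistical analysis plan was not available for this review, but an analysis plan could not repair this point: it cannot recover data that were not collected.

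**Working it through.** **Inputs, all from the Protocol**

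- Serious-event window after ring use: 7 days (11.1.1).
- End of adverse-event collection: final ring removal visit (10.1.3).
- Final removal: week 12 in group A, week 13 in group B; last visit: week 14 (8.1.8).
- Visit windows: group A removals up to 2 days late, group B visits 3 days either way (8.1.3); last visit 3 days either way (8.1.4).
- End-of-trial qualitative sample: one discussion group of 8-12 women and 3-5 interviews per randomization group (7.3).

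**1. Calendar.** Take day 0 as enrolment at the start of week 1, so that week k falls on day 7 × (k − 1).

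- Group A final removal: 7 × 11 = day 77.
- Group B final removal: 7 × 12 = day 84.
- Week-14 visit: 7 × 13 = day 91.

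**2. Required against planned.** The endpoint needs 7 days after the final removal; planned collection gives 0 days in both arms.

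- Group A: the window ends on day 77 + 7 = 84, so the uncovered share is 7/84 = 8.3%.
- Group B: the window ends on day 84 + 7 = 91, so the uncovered share is 7/91 = 7.7%.

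If all 120 women completed, this would be 120 woman-weeks. That is an upper bound, because some women will be lost or will withdraw consent.

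**3. Earlier ring-free weeks in group A.** Section 8.1.3 lists for the ring insertion visits: "Information on adverse events, social harms and concomitant medication will be collected". V3 and V5 therefore cover the weeks after rings 1 and 2. Only the week after the last ring lacks planned collection.

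**4. Would an added question at week 14 be enough?** Interval from final removal to the last visit:

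| | Shortest | Nominal | Longest |
|---|---|---|---|
| Group A | (91 − 3) − (77 + 2) = 9 days | 14 days | (91 + 3) − 77 = 17 days |
| Group B | (91 − 3) − (84 + 3) = 1 day | 7 days | (91 + 3) − (84 − 3) = 13 days |

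The schedule table prints the group B and week-14 windows as +3 days only. On that reading the group B interval is 91 − 87 = 4 to 94 − 84 = 10 days. On either reading the visit always falls after the 7 days in group A but can fall inside them in group B.

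**5. How many women might need another contact?** If only the qualitative sample attends week 14, and discussion and interview participants are different women, attendance is 2 × (8 to 12) + 2 × (3 to 5) = 22 to 34 women. That leaves 120 − 34 = 86 to 120 − 22 = 98 women (72% to 82%) not seen, plus any group B attenders seen before day 7.

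**The case against.** The best defence is that the two sections can be read together. Ending routine collection at the last removal is exactly what the first half of endpoint 4 needs. Serious events have their own section, 10.1.5, which requires reporting within 24 hours and sets no end date, and section 10.2 sends these reports to the safety monitor as they occur. Section 10.1.3 asks women to tell staff about medical problems while in the study and gives them contact details. Section 8.1.5 allows unscheduled visits at any time. Section 7.5 provides safety follow-up for women discontinued for safety reasons.

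Much of this stands. A reader might infer that the last week is wholly unobserved, or that no serious event in it could reach the monitor. The documents do not support that: passive reporting exists, and women stopped for safety reasons have some follow-up, though of unstated length.

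These provisions do not close the gap, however. The 24-hour rule governs how fast a known event is passed on, not how it is found. Following adverse events to resolution concerns events already recorded. And because a serious event is defined as an adverse event, the cut-off in 10.1.3, read literally, would exclude a late report.

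It is also fair to say that a zero count would not show safety even with full ascertainment: zero events in 120 women leaves an upper 95% limit of about 3/120 = 2.5%. The case for a change is therefore that the endpoint should be collected as defined, not that doing so would settle the safety question.

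**Conclusion.** The point holds in limited form. Sections 10.1.3 and 8.1.8 do not provide the collection that 11.1.1 requires: the 7 days after the last ring, about 8% of the nominal serious-event window in each arm, have only passive reporting. The expected consequence is some undercounting of serious events in one secondary safety endpoint.

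A reader might go further and infer a biased comparison between groups. The documents do not support this: the uncovered stretch is 7 days in both arms and group A's earlier ring-free weeks are covered, so the gap does not by itself create an imbalance. The primary endpoint and the sample size are unaffected.

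The percentages assume the nominal calendar and women who complete ring use. The conclusion also assumes that the cut-off in 10.1.3 applies to serious events. The definition in 10.1.5 supports that and no section says otherwise, but the text could be read as leaving serious-event reporting open-ended. Even on that reading no contact is scheduled at which the events would be asked about.

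**What to change.** Reconcile 10.1.3 and 8.1.8 with 11.1.1:

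- State in 10.1.3 that serious adverse events are collected until 7 days after the last ring removal. Include women who discontinue early, except those who withdraw consent, for whom section 7.5 allows no further procedures. Collection of other adverse events can still end at final removal, since the endpoint needs no more.
- Add a serious-event question to the week-14 row of 8.1.8 for both groups.
- Provide a brief telephone contact, at or after day 7, for women who do not attend week 14 and for those seen less than 7 days after their actual removal, which can happen in group B. Early discontinuers need the same contact timed from their own removal.

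The cost is a change of wording, one CRF item and a short call. The calls should be budgeted realistically: sections 8.1.4 and 8.1.8 leave unclear whether all women come at week 14, and if only the qualitative sample does, 86 to 98 of 120 women would need one.

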#### **10.1.4. Pregnancy outcomes**

Should a participant become pregnant during the study, she will be followed up by the study team until delivery, and the pregnancy outcome will be collected and documented. Any pregnancy outcomes that meet criteria for SAE reporting (e.g. congenital anomalies) occurring among participants will be reported as SAEs to the concerned bodies and included in the study report.

#### **10.1.5. Serious Adverse Events (ICH E6, Section 1.50)**

An SAE is any adverse event/experience occurring at any study drug dose that results in any of the following outcomes:

- Death;
- Life threatening (subject at immediate risk of death);
- Requires in-patient hospitalization or prolongation of existing hospitalization;
- Results in congenital anomaly/birth defect;
- Results in a persistent or significant disability or incapacity.

An important medical event that may not result in death, be life threatening, or require hospitalization may be considered an SAE when, based upon appropriate medical judgment, the event may jeopardize the subject and may require medical or surgical intervention to prevent one.

There may be situations when an SAE has occurred and the investigator has minimal information to include in the initial report to the Sponsor. However, it is very important that the investigator always makes an assessment of causality for every event prior to transmission of the report to the Sponsor according to the definitions in section 10.1.2. The investigator may change his/her opinion of causality in light of follow-up information, amending the SAE-report form accordingly.

All SAE's whether or not deemed drug related or expected must be reported immediately or within 24 hours (one working day) using the SAE Notification Form by telefax or email to:

**Clinical Trials Unit**  
**Institute of Tropical Medicine**  
**[name]**  
**[name]**  
**[contact]**  
**Email: [contact]**

Line listings of all reported SAEs will be sent to the IRB of the ITM and the EC of UZA annually. All SAEs will be sent to the Rwanda National Ethics Committee case by case. RU will also submit annual line listings of all AEs to the Rwanda National Ethics Committee.

## **10.2. Data and Safety Monitoring Board**

Due to the expected short recruitment period and the use of commercially available and approved CVRs, no formal Data Safety Monitoring Board (DSMB) will be set up. However, an independent data safety monitor (gynecologist) will be appointed who will receive, as they occur, and review all SAE reports with special attention to cardiovascular events (for example venous thrombosis) which may be associated with the use of hormonal contraception. In case of major safety concerns, this independent safety data monitor may request the sponsor to halt recruitment of the trial and/or to organize a formal DSMB with a complete overview of all available safety data.

## **11. ANALYSIS METHODS**

### **11.1. Clinical Data**

The statistical analysis of the primary objective and secondary objective 1 of the clinical trial will be performed by the study statistician at the CTU (ITM) according to a Statistical Analysis Plan which will be approved before database lock. The statistical analysis of secondary objectives 2 and 3 will be done by PhD student, at the ITM and at RU/UoL respectively, under the guidance of statisticians at the ITM and UoL. As these analyses will be research and data driven, no prior statistical analysis plan will be made but the statistical analysis methods will be fully described in the resulting reports and/or publications.

